**Figure 1 figure1:**
[figure not shown]
CONSORT (Consolidated Standards of Reporting Trials) flow diagram of participant recruitment, randomization, and attrition.

After randomization, the wait-list group will be informed that they are in the wait-list control group on REDCap. The intervention group will be shown a link and instructions on how to download the Whitu app on REDCap. During the first four weeks, participants in the intervention group will receive 2 emails reminding them to complete the app modules and an SMS text message asking them to confirm whether they have been able to download the app. Four weeks after completing the baseline questionnaires, participants in both groups will receive an email with a link to the first follow-up questionnaire on REDCap. Three months after baseline, both groups will receive an email with the link to the final follow-up assessment. After the wait-list control group completes the 3-month assessment, REDCap will send each group member an automated email with instructions on how to download the Whitu app. We will not follow up with the wait-list control group after they receive the app at the 3-month time-point.

All participant outcome data (eg, demographic data and psychological outcomes) will be collected via REDCap. We will not collect any information via the app, and any user input (eg, first name, responses to exercises) will only be stored locally on the user’s device. Only the Principal Investigators and research assistants ([name]) will have access to the participant data collected over REDCap. When the data are exported from REDCap, all data will be deidentified and stored separately from the participants’ information.

### Power Calculation

A previous study of a web-based positive psychology intervention for mildly depressed adults [44] found a between-group improvement in well-being (effect size of *f*=0.155) using the World Health Organization-Five Well-Being Index (WHO-5) [45]. Using G*Power [46], we calculated that the minimum required sample size to detect an effect size of *f*=0.155 using a mixed analysis of variance (ANOVA) including within-subject (3 time points) and between-subject (2 groups) effects with 90% power and at a 2-sided 5% significance level was 90 participants (45 per treatment arm). To ensure cultural acceptability, we will aim to recruit at least 40% Māori and Pacific young people (n=36).

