#### Primary Outcomes

##### 1. Emotional Well-Being

This outcome will be assessed via the WHO-5 [45]. The WHO-5 is a 5-item scale that assesses positive emotional well-being (eg, “I have felt cheerful and in good spirits”). Participants are asked to indicate the extent to which each item matches how they have been feeling over the past two weeks on a 6-point Likert scale ranging from 0 (“at no time”) to 5 (“all of the time”). The final score is calculated by summing the five responses and multiplying the total by four. This gives a percentage score ranging from 0-100, with 0 representing the worst possible well-being and 100 representing the best possible well-being. The internal consistency of the WHO-5 demonstrates good reliability (α=.84) in children and adolescents [49].

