##### 2. Mental Well-Being

This outcome will be assessed by the Short Warwick-Edinburgh Mental Well-being Scale (SWEMWBS) [50,51]. The SWEMWBS is a short version of the 14-item Warwick-Edinburgh Mental Well-Being Scale (WEMWBS), which is comprised of positively worded items measuring different aspects of positive mental health [41]. The SWEMWBS is a 7-item scale that asks participants to rate their experience of a range of thoughts and feelings (eg, “I’ve been dealing with problems well”) over the last two weeks on a 5-point Likert scale ranging from 1 (“none of the time”) to 5 (“all of the time”). The score is calculated by summing individual ratings and transforming the total into a metric score using a transformation provided by the scale authors. Scores range from 7 to 35, with higher scores indicating greater positive mental well-being. The original scale has demonstrated good content validity and is correlated with other mental health and well-being measures [50]. The short version has demonstrated similar reliability and validity to the full version (α=.84) and is suitable to be used by adolescents [52,53].

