#### Hypotheses and Statistical Analyses

It is predicted that the Whitu app group will demonstrate improved well-being (increased emotional and mental well-being), increased self-compassion, and improved sleep at 4-week and 3-month follow-up compared to the wait-list control group. We also hypothesize that the Whitu app group will demonstrate decreased stress, depression, and anxiety at 4-week and 3-month follow-up compared to the wait-list control group.

Data will be analyzed in SPSS (IBM Corporation) or SAS (SAS Institute). Prior to any data analysis, the data will be tested for violations of statistical assumptions and screened for errors and outliers. If parametric assumptions are not met due to nonnormality, transformations or nonparametric tests will be used. Pearson correlations (or Spearman ρ if nonnormal) will be used to explore the relationships between the outcome measures and demographic characteristics and other psychosocial factors. ANOVAs or Kruskal-Wallis tests (if nonnormal) will be used to explore associations between categorical variables and outcome measures. Linear mixed models will be used to determine whether changes in psychological outcomes are the result of the interaction between the intervention group and time, with post-hoc tests to assess pairwise comparisons of groups at each time point and within-group changes over time. Linear mixed models also allow for missing data, as they enable all participants with baseline data to be included in the analysis. We will also examine possible 3-way interactions with age, sex, or ethnicity (eg, age*group*time). Means, SDs, and CIs will be presented with the analysis. Data will be subjected to both intention-to-treat and per-protocol analyses. Per-protocol analyses will include participants who report completing all seven modules. Study results will be disseminated through peer-reviewed journals and conferences.

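### Two unranked primary outcomes with no either/both success rule, while N=90 gives the stated 90% power at 5% for one WHO-5 test only

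*Protocol article*

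**What the plan says.** Under Primary Outcomes, the protocol article has two numbered entries. For emotional well-being: "This outcome will be assessed via the WHO-5 [45"]. For mental well-being: "This outcome will be assessed by the Short Warwick-Edinburgh Mental Well-being Scale (SWEMWBS"). The numbering is not described as a testing order.

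Under Hypotheses and Statistical Analyses, the app group "will demonstrate improved well-being (increased emotional and mental well-being), increased self-compassion, and improved sleep at 4-week and 3-month follow-up". No rule says whether one or both primary outcomes must succeed. The same section analyses each outcome with a linear mixed model aimed at the group-by-time interaction. Comparisons of the groups at each time point are described as post hoc.

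Under Power Calculation, the effect size comes from one earlier study, measured "using the World Health Organization-Five Well-Being Index (WHO-5"). The calculation gives the "minimum required sample size to detect an effect size of *f*=0.155" for a mixed ANOVA "including within-subject (3 time points) and between-subject (2 groups) effects", "with 90% power and at a 2-sided 5% significance level was 90 participants". No effect size, significance level or power is given for SWEMWBS.

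**The concern.** The protocol gives two outcomes primary status and sizes the trial for one test on one of them. These statements fit together only if something ranks the outcomes or defines primary success, and nothing shown does.

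As written, the trial could report a primary success on WHO-5, on SWEMWBS or on both, each judged at 5%. A reader would naturally take the 5% and the 90% as properties of the primary objective. At stake is either a false-claim rate above 5% or power below 90%, depending on which success rule is applied once results are known.

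**Working it through.** **Inputs from the Power Calculation section:** f = 0.155, two-sided 5%, power 90%, k = 2 groups, m = 3 time points, N = 90 (45 per arm).

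**Assumed, because not stated:** correlation between repeated measures ρ = 0.5; sphericity (ε = 1).

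**Step 1. Reproduce the plan's figure.** For the within-between interaction:

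- λ = f²·N·m/(1−ρ) = 0.024025 × 90 × 3 / 0.5 = 12.97
- df1 = (k−1)(m−1) = 2; df2 = (N−k)(m−1) = 88 × 2 = 176
- critical F at 5% = 3.047; power = 90.2%

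At N = 88 power is 89.5%, so 90 is the smallest even total. Other readings do not give 90: the between-groups main effect needs 294, the alternative (SPSS-type) effect-size definition needs 268, and the interaction at ρ = 0.3, 0.4, 0.6 or 0.7 needs 126, 108, 72 or 56. The stated figure is therefore correct for one WHO-5 interaction test.

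**Step 2. Success on either outcome, one interaction test each at 5%.** If the tests are independent, the error rate is 1 − 0.95² = 9.75%. Simulating two 2-df tests with a between-outcome correlation (assumed; the article gives none):

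| Correlation | Chance of at least one false claim |
|---|---|
| 0 | 9.8% |
| 0.5 | 9.2% |
| 0.7 | 8.5% |
| 0.8 | 8.0% |

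**Step 3. Repair by splitting alpha to 2.5% each.** Same λ and degrees of freedom; critical F = 3.767. Power at N = 90 is 84.4%. Restoring 90% needs N = 106 (53 per arm). This depends on ρ:

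| ρ | Power at N = 90, 5% | Power at N = 90, 2.5% | N for 90% at 2.5% |
|---|---|---|---|
| 0.3 | 77.6% | 68.3% | 146 |
| 0.5 | 90.2% | 84.4% | 106 |
| 0.7 | 99.0% | 97.9% | 64 |

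**Step 4. Success on both outcomes required.** The error rate stays at or below 5%. Assuming 90% power for each outcome, joint power is 0.9 × 0.9 = 81% if independent. By simulation (normal approximation) it is 83.2%, 84.7% and 85.6% at correlations 0.5, 0.7 and 0.8. The 90% for SWEMWBS is itself an assumption.

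**Step 5. Fixed order, WHO-5 then SWEMWBS, each at 5%.** SWEMWBS is tested only after a significant WHO-5 result, so the chance of any false claim across the two stays at or below 5%. The WHO-5 test is the one in Step 1, so its 90.2% is unchanged.

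**Step 6. Does it matter which WHO-5 test comes first?** The powered test covers all three time points. Hold the interaction at f = 0.155 with ρ = 0.5 and 45 per arm. For the change from baseline to 4 weeks, the standard error in SD units is √(2(1−ρ) × 2/45) = 0.211.

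- Effect complete by 4 weeks and then held: difference = 0.155 × √18 = 0.658; ratio to SE 3.12; power about 87%.
- Half the effect by 4 weeks and the rest by 3 months: difference at 4 weeks = 0.155 × √24 / 2 = 0.380; ratio 1.80; power about 43%.

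The WHO-5 power is preserved only if the interaction, not a 4-week contrast, is tested first.

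**The case against.** The strongest reply is that the power statement describes one test and is right for it. The article never says that 5% is a trial-wide error rate or that 90% covers both outcomes. It is also a condensed document: multiplicity rules often sit in an analysis plan, which is not shown, and the trial aims only at preliminary effectiveness, with a larger and more definitive study to follow.

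Much of this stands. The missing adjustment rule is not in itself the finding, and the preliminary aim makes the matter less grave. What remains is what the article does fix: two primary outcomes, directional hypotheses on both, and a sample size that gives the full 5% to one.

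Three stronger readings are tempting but not supported:

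- *Either the 5% or the 90% must be wrong.* This is not exhaustive. A stated order, or WHO-5 as the single primary outcome, keeps both figures at N = 90.
- *Two outcomes at two time points make four primary tests.* That would give 1 − 0.95⁴ = 18.5% if independent, or roughly 13–17% for the correlations tried. But the plan tests each outcome with one interaction spanning both follow-ups and labels the time-point comparisons post hoc. The four-test figures apply only if those comparisons are presented as stand-alone primary claims.
- *Power falls to about 74%.* That figure combines the 2.5% split with an assumed 20% loss to N = 72. The article gives no attrition rate, and at N = 72 with 5% power is already 82%, so about half of the fall has nothing to do with multiplicity. It also treats dropouts as wholly lost, although the planned mixed model keeps everyone with baseline data.

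**Conclusion.** The point holds in a limited form. The power statement is correct for a single WHO-5 interaction test, but the two declared primary outcomes are neither ranked nor joined by a success rule, so the 5% and 90% do not yet describe the primary objective. Under an either-outcome rule the inflation is about 1.6 to 2 times the nominal 5%. Under a both-outcomes rule the shortfall is in power, by about 4 to 9 percentage points.

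The power figures rest on ρ = 0.5 and sphericity. That ρ is inferred because it is the only value tried that returns 90. The error rates depend on an assumed between-outcome correlation of 0 to 0.8, and the joint power on the assumption that SWEMWBS is as well powered as WHO-5. This should be corrected; it does not invalidate the design.

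**What to change.** Before analysis, state that:

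1. The first primary test is the WHO-5 group-by-time interaction, two-sided 5%. This is the test that the Power Calculation section sizes.
2. The SWEMWBS group-by-time interaction is tested at two-sided 5% only if the WHO-5 test is significant.
3. The 4-week and 3-month group comparisons are follow-up estimates with confidence intervals, not stand-alone primary claims.

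It would also help to record the correlation and sphericity assumptions behind N = 90. If an analysis plan already sets an order, the protocol should be aligned with it.

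The cost is a few sentences and a registry note, with no added participants. The downside is that a benefit on SWEMWBS cannot be claimed as confirmed if WHO-5 is not significant. The chance of claiming both remains the 81–86% of Step 4, under the same assumption about SWEMWBS.

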**Methods:**

A two-phase mixed methods study will be undertaken to achieve these aims. During the first phase, 20 young people aged 16-30 years (including those of Māori and Pacific ethnicity) will participate in a qualitative study to help refine the prototype app. During the second phase, 90 young people aged 16-30 years will participate in a randomized waitlist-controlled trial (RCT) to evaluate the efficacy of the refined Whitu app at 4 weeks and 3 months after baseline. Outcomes will be evaluated using validated web-based questionnaires at baseline, 4 weeks, and 3 months.

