## Discussion

### General Considerations

Through this mixed-methods study, we hope to develop a coping skills app for young people in New Zealand aged 16-30 years to use during and immediately following the COVID-19 pandemic and to provide preliminary evidence of its acceptability and effectiveness at improving well-being and other mental health outcomes. As young people of Māori and Pacific ethnicity are already at greater risk of developing psychological problems such as anxiety and depression, we hope the app is particularly appealing and useful for young people in these groups. As the app is based on proven strategies and techniques for improving psychological well-being, we hope it will also be of longer-term value to its users.

Limitations of this study may include low adherence and attrition, which we have attempted to minimize by framing the intervention as a resource that can be completed within seven days. Another possible limitation is that we are only assessing self-reported user engagement. In future prototypes, we hope to also include app analytics to explore more objective measures of user engagement. Lastly, as the app is tailored to New Zealand youth aged 16-30 years, we will not be able to generalize our findings to people younger than 16 years or those outside New Zealand. However, if the app is effective in improving well-being, we hope to conduct a larger and more definitive study in the future that includes younger participants and those outside New Zealand.

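### The 90 participants planned for the trial equal the no-loss minimum for 90% power, so the stated power leaves no room for the attrition that the article names as a possible limitation

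*Protocol article*

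**What the plan says.** The Power Calculation section describes 90 as "the minimum required sample size to detect an effect size of *f*=0.155" in a mixed ANOVA "including within-subject (3 time points) and between-subject (2 groups) effects", for 90% power. The requirement "at a 2-sided 5% significance level was 90 participants (45 per treatment arm"), and it is followed by a Māori and Pacific recruitment target of 40%, given as 36 people. Since 36/0.40 = 90, that target is also taken on 90 recruited.

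The Methods paragraph of the abstract plans the same number: "90 young people aged 16-30 years will participate in a randomized waitlist-controlled trial (RCT").

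Under Phase 2, Procedures, participants are randomised after the baseline questionnaires. Loss therefore falls on the 4-week and 3-month data.

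The Discussion (General Considerations) says: "Limitations of this study may include low adherence and attrition". It adds that the authors tried to limit this by making the app completable in seven days. The text gives no attrition rate.

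On missing data, the section Hypotheses and Statistical Analyses says: "Linear mixed models also allow for missing data, as they enable all participants with baseline data to be included in the analysis".

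**The concern.** A mixed ANOVA power calculation takes every participant to be measured at every time point. Its minimum is thus a number of completers, and here that number is also the number to be enrolled. Any loss after randomisation takes the trial below its stated power. Recruitment is through social media and the follow-up questionnaires are sent as emailed links up to 3 months after baseline, so some loss is plausible.

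What is at stake is how a null result will be read. A reader who takes the 90% at face value will treat a non-significant WHO-5 result as stronger evidence against an effect of the assumed size than the trial can supply.

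**Working it through.** **Inputs from the article:** f = 0.155, k = 2 groups, m = 3 time points, two-sided 5% level, 90% power, N = 90.

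**Inputs assumed here, because the article does not state them:** correlation between time points ρ = 0.5, sphericity (ε = 1), and all loss rates.

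**Step 1: reproduce the 90.** For the within-between interaction:

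- λ = f² · N · m · ε / (1 − ρ) = 0.024025 × 3 / 0.5 × N = 0.14415 N
- df1 = (k − 1)(m − 1) = 2; df2 = (N − k)(m − 1) = 2(N − 2)
- at N = 90: λ = 12.97, df2 = 176, critical F = 3.05, power = 90.2%
- at N = 89: 89.9%; at N = 88: 89.5%

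The figure of 90 is reproduced and is the smallest N that reaches 90%. Alternatives do not reproduce it: the between-group main effect needs 294, and the interaction with ε = 0.75 needs 110.

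**Step 2: sensitivity to the unstated correlation, no loss.** With ρ = 0.6 the minimum is 72. With ρ = 0.4 it is 108 (equal arms), and 90 would then give only 84.0% even with complete data.

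**Step 3: completers only, ρ = 0.5.** The same formula with N reduced:

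| Assumed loss | Completers | λ | Power |
|---|---|---|---|
| 0% | 90 | 12.97 | 90.2% |
| 10% | 81 | 11.68 | 86.7% |
| 20% | 72 | 10.38 | 82.2% |
| 30% | 63 | 9.08 | 76.4% |
| 40% | 54 | 7.78 | 69.2% |

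**Step 4: approximate power of the planned mixed model, which keeps partial data.** Loss is taken as monotone and equal in both arms, with a share d1 gone by 4 weeks and d2 by 3 months, and compound symmetry with ρ = 0.5. The information on the three time-point means is summed over people seen three times, twice and once. V is the resulting covariance of the group differences, L takes changes from baseline, and δ is a pattern of group differences scaled to an interaction f of 0.155.

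- λ = (Lδ)′(LVL′)⁻¹(Lδ)
- df2 = 2(N − 2) − N(d1 + d2), which is 176 − 27 = 149 for losses of 10% and 20%, and 176 − 45 = 131 for 20% and 30%

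| Group difference at baseline, 4 weeks, 3 months (relative) | No loss | 10% then 20% | 20% then 30% |
|---|---|---|---|
| 0, 1, 1 | 90.2% | 87.0% | 83.6% |
| 0, 1, 0.5 | 90.2% | 87.6% | 84.2% |
| 0, 1, 0 | 90.2% | 86.1% | 81.8% |
| 0, 0.5, 1 | 90.2% | 84.8% | 80.6% |
| 0, 0, 1 | 90.2% | 83.0% | 77.8% |

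The no-loss column agrees with step 1. The ranges are about 83-88% and about 78-84%. The low end is the pattern in which the effect appears only at 3 months, where the missing data fall on the time point that carries it.

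**The case against.** Several counter-arguments are sound and limit the point.

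- **The calculation is not wrong.** A reader might infer an arithmetic error, but 90 reproduces exactly. The fault lies in using a no-loss minimum as the enrolment figure while stating its power without a condition.
- **The correlation of 0.5 is inferred.** It was chosen here because it returns 90. If the true value were 0.6, then 72 completers would suffice and 90 could lose 20% and still hold 90%. This stands, but it cuts both ways (step 2), and the article claims no such reserve.
- **Completers-only figures describe a different analysis.** It is tempting to quote 82% as the power at 20% loss. For the planned mixed model that is a floor, approached only when all the loss has occurred by 4 weeks.
- **Attrition is not forecast.** The Discussion says limitations may include it, so one cannot say that the authors expect it. The decline is also gradual: one missing participant costs about 0.3 percentage points (90.2% to 89.9%).
- **The missing-data sentence is not an error.** A reader might take it as a claim that mixed models preserve power. It says only that everyone with baseline data enters the analysis. A person with baseline data alone adds almost nothing on the group-by-time effect, but the sentence does not say otherwise.
- **Retention incentives.** Because the wait-list arm receives the app after its 3-month assessment, a reader might infer that only that arm has a reason to stay. The article gives participants a voucher for taking part and does not say when it is paid, so this is not supported.
- **Aim and source.** The trial seeks preliminary evidence and foresees a larger study. Figure 1 and the full protocol are not shown and might hold a retention assumption, although a total of 90 in both the abstract and the power section makes an inflated target unlikely.

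None of this alters the fact that, as the article stands, the minimum and the planned number coincide and the 90% is given without a condition on follow-up.

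**Conclusion.** The point holds in a moderate form. The sample size is correctly calculated, but it contains no margin for loss after randomisation, so 90% is the power at full follow-up. At 20% loss by 3 months, power for the planned analysis would be about 83-88% if half of that loss had occurred by 4 weeks, with 82% as the completers-only floor. With 20% lost by 4 weeks and 30% by 3 months it would be about 78-84%. All these figures assume f = 0.155, a correlation of 0.5, sphericity, and monotone loss that is equal in both arms; the loss rates are illustrative. The shortfall is a few points at modest loss and becomes material only at heavier loss. It is a matter of stating the power honestly, and does not make the trial unsound.

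**What to change.** In the Power Calculation section, make three short changes:

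1. State that 90 is the number required with complete data and includes no allowance for attrition.
2. State the correlation (and sphericity) assumed in the calculation.
3. Restate the power for 90 randomised as a range at a named retention, for example: *about 82-88% if 20% are lost by 3 months, assuming a correlation of 0.5 between time points*. The lower figure is the completers-only floor and the upper is the most favourable mixed-model pattern above with 10% lost by 4 weeks.

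The missing-data sentence and the voucher arrangements need no change for this purpose. The cost is a slightly less favourable stated figure, with no extra participants or money. Should the sponsor prefer to keep 90% at an assumed 20% loss on the completers-only basis, 90/(1 − 0.20) = 112.5, so 113 (114 for equal arms) would have to be randomised. That would be a real cost, and the correction does not depend on it.
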